Drawing on previous research and theories on social networks and translation of information contagion into attitudes and behaviors, several network characteristics which may influence the delivery of primary care for CVRM by health professionals and self management of patients at risk for CVD and with established CVD can be inferred. For a schematic representation of the hypothesized relations see Figure 1. For healthcare professionals we expect a number of social network characteristics to be of importance. Firstly, a high density (the proportion of all possible connections in a given network that are actually present) is expected to be beneficial as it provides multiple opportunities for various social influence mechanisms, such as for example imitation of successful behaviors and social comparison [8,16,17]. Secondly, a high frequency of contacts (within existing relationships) is expected to be important, as this enhances social influence and offers protection against egocentric choices [16,18,19]. Thirdly, high homogeneity of individuals in a network (e.g. regarding educational background) is expected to enhance social comparison uptake of information items that are disseminated in the network [20]. Fourthly, individuals with high centrality in a social network are expected to be influential as they have many connections and high centrality has been associated with enhanced knowledge transfer [21,22]. In healthcare, individuals with high centrality are expected to be present in social networks as CVRM-coordinators or case managers. Both are purposefully created to become highly central individuals in healthcare delivery networks. Fifth, an informal opinion leader may be identifiable in a network. He or she represents a person who influences opinions, attitudes, beliefs, motivations, and behaviors of others [23]. For these network-related factors, it may be noted that the direction of the social influence (e.g. better or worse CVRM) depends on the content of the information that is shared.

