**Health outcomes** Health outcomes will consist of SBP, cholesterol, and risk score. Thresholds for desired treatment values for SBP and cholesterol may differ for patients at risk, with established CVD, patients of certain ages, and according to individual targets set in agreement with treating health professionals and will be analyzed accordingly. Risk scores, only applicable to patients without established CVD, will be calculated using prevailing risk estimation tables [36]. The following parameters will be used in the calculation: age, gender, smoking status, systolic blood pressure (SBP) and total cholesterol/HDL-cholesterol ratio. The Epa Cardio abstraction tool [31] for medical audit will be used for abstracting these health outcomes.

#### **
*Other measures on patients will include*
**

##### 

**Descriptive variables** Descriptive measures will include age, sex, ethnicity, marital status, educational level, and social economic status (SES). For data collection we will use a questionnaire containing items from the Epa cardio abstraction tool [32].

##### 

**Information items for constructing social networks** For constructing and measuring social networks, patients are asked to indicate on a network roster from which persons they have received information on 1) medical treatment, 2) handling their condition or disease, and 3) practical help. We will provide a specifically developed and personalized roster questionnaire with names and disciplines of health professionals from their general practices (see Additional file 3: Appendix 3a). Patients are offered the possibility to add names of other persons (healthcare professionals/people in personal circle) they have received information from.

Alters are asked to indicate on a network roster to which persons they have provided information on 1) medical treatment, 2) handling their condition or disease, and 3) practical help using a specifically developed and personalized roster questionnaire (see Additional file 3: Appendix 3b).

##### 

**Frequency of contact** For measuring frequency of contact, patients will be asked to indicate how often they have received information from persons who have provided information in the last year. Similarly, alters will be asked how often they have provided information.

##### 

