### Sample size calculation

The RCT study, in which the present research is embedded, is powered to detect a 15% difference in provided personalized lifestyle advice by including 900 patients clustered within 30 practices [30]. For the present research, we calculated the sample size for detecting a 15% difference in response rate of patients who are approached by 1) an invitation for participation in this study with a telephone interview) and 2) the choice for participating by a telephone interview or a paper-based test. Assuming alpha is 0.05, power of 0.80, a response rate of 50% in the first group and 65% in the second group, we estimated that we need to include 338 patients.

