### Statistical analyses

Response rates for health professionals and patients will be determined. For patients we will compare response rates between the patient group invited by either a single option for participation and the group that will be offered the choice to participate by either a telephone interview or a paper-based test in order to assess which method is most feasible for including them in social network research using *X*^2^ tests.

Reliability of reported social network connections will be investigated by examining the proportion of all possible connections that will be mutually reported present or absent (reciprocity coefficients in non-directed networks). In accordance with guidelines on handling missing values, we will substitute these by values as provided by responses of other individuals. In case of no information on connections, we will indicate no contact by a filling in a zero in the data [41].

For describing social networks of health professionals and patients we will compute network parameters and provide visualization by using graphic displays. Random permutation tests will be used for comparisons of network characteristics.

For testing our hypotheses and further explorative analyses, controlling for potential confounders, we will use multivariate logistic regression models to investigate the effect of social networks characteristics on professional performance of practice nurses and patients’ self-management and health outcomes.

In the analysis of professional performance of practice nurses regression models will include six network characteristics (density, frequency of contact, homogeneity, presence of informal opinion leaders and CVRM-coordinators, and centrality) as predictors of main interest. As control variables we will include trial arm (intervention vs control group), personal characteristics (amongst others education, years of experience in profession), and practice characteristics (practice size, involvement in other projects or organizations).

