In the analyses of self-management and health outcomes in patients, several multivariate logistic regression models will be estimated. For self-management, separate models will be estimated on physical activity, diet, and smoking. For health outcomes, separate models will be estimated on SBP, cholesterol, and risk score. Models will include four network characteristics as predictors: number of alters with favorable health behaviors, who are also connected among each other, number of alters with depressive symptoms, and number of alters who can provide CVRM-related information. The regression models will be controlled for trial arm (intervention vs control group), patient group (high risk or established CVD), and several personal characteristics: age, sex, ethnicity, marital status, SES, patient activation, therapy adherence, and depressive symptoms.

Two approaches will be used to investigate effects of social network characteristics on change in professional performance of practice nurses and self-management and health outcomes of patients after the intervention period at six month follow-up. First, follow-up outcomes measures will be treated as dependent variables. We will estimate similar models as described above and include baseline measures of outcomes of interest as predictors. Second, we will consider change as the difference between the baseline- and follow-up measures of the diverse outcomes of interest. Ordinal logistic regression models will be estimated, with change represented in three categories; a shift from inadequate to adequate outcomes, no change, and shift from adequate to inadequate outcomes.

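### Educational level is planned as a patient measure separate from SES but is missing from the patient-model covariates, so some confounding by education may remain in the network coefficients

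*Protocol article*

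**What the plan says.** Under Primary outcomes for patients (Descriptive variables), the Protocol article lists the patient descriptors: "Descriptive measures will include age, sex, ethnicity, marital status, educational level, and social economic status (SES"). They come from patients by questionnaire: "For data collection we will use a questionnaire containing items from the Epa cardio abstraction tool". Education and SES are two items in that list. SES is not defined there or elsewhere in the article.

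Under Statistical analyses, the stated purpose of the models is confounder control: "controlling for potential confounders, we will use multivariate logistic regression models to investigate the effect of social networks characteristics". There are separate patient models for physical activity, diet, smoking, SBP, cholesterol and risk score. On the predictors: "Models will include four network characteristics as predictors: number of alters with favorable health behaviors, who are also connected among each other", followed by alters with depressive symptoms and alters who can supply CVRM information. The models control for trial arm, patient group and "several personal characteristics: age, sex, ethnicity, marital status, SES, patient activation, therapy adherence, and depressive symptoms". This list has no open-ended wording.

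The models for practice nurses' performance, in the same section, use "personal characteristics (amongst others education, years of experience in profession").

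**The concern.** Education is a standard candidate confounder here. It plausibly affects a patient's own smoking, diet and activity. It also plausibly affects who is in the patient's circle: how many contacts live healthily, whether those contacts know each other, and how many have medical training. A model that leaves it out can show an association between healthy alters and healthy patients with no influence passing between them.

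The article's own theory points this way. It names selection of contacts among the drivers of contagion, and its example of similarity within networks is education: "high homogeneity of individuals in a network (e.g. regarding educational background"), although that sentence concerns professionals.

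At stake are three of the four patient network predictors and the reading of the patient hypotheses. The Discussion wants the results to inform later interventions on self-management, so it matters whether an association reflects influence or resemblance.

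**Working it through.** **1. The two lists side by side.**

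| Patient descriptor collected | In patient models? |
|---|---|
| Age | yes |
| Sex | yes |
| Ethnicity | yes |
| Marital status | yes |
| Educational level | **no** |
| SES | yes |

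The models add patient activation, therapy adherence and depressive symptoms. Five of six descriptors carry over; education alone does not.

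**2. Is there a planned figure to reproduce?** Not on this point. The only sample size calculated for this study concerns response to the invitation: "Assuming alpha is 0.05, power of 0.80, a response rate of 50% in the first group and 65% in the second group", giving 338 patients. A two-sided comparison of two proportions without continuity correction gives 170 per group, 340 in total, which agrees closely but does not bear on the covariates. Only its response rates are used below, to assume a number of network participants: 0.50 × 900 = 450 and 0.65 × 900 = 585.

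**3. What decides the size.** The inputs are assumed, because the documents give none. Let r be the correlation of education with the alter measure, ρ the correlation of education with SES, and OR_E the odds ratio of education for the outcome. Suppose there is no true alter effect, and SES is related to the alter measure only through education. With SES adjusted and education omitted, the share of the education effect that moves onto the alter measure (per SD of each) is approximately

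b = r(1 − ρ²) / (1 − r²ρ²), and spurious OR ≈ exp(b × ln OR_E).

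Example: r = 0.3, ρ = 0.5, OR_E = 2.0 per SD. b = 0.3 × 0.75 / (1 − 0.0225) = 0.230, and exp(0.230 × 0.693) = 1.17. A logistic simulation with 200,000 subjects gives 1.155. The formula runs slightly high at larger effects.

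Simulated spurious OR per SD of healthy alters, for OR_E 1.3 to 2.0 and r 0.2 to 0.3:

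| SES–education correlation | Spurious OR per SD |
|---|---|
| SES not in model | 1.04–1.21 |
| 0.5 | 1.04–1.16 |
| 0.7 | 1.03–1.11 |
| 0.9 | 1.01–1.04 |
| 1.0 (SES contains education) | 1.00 within simulation error |

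**4. On the scale of one healthy alter.** Assume up to four alters, 40% of patients with higher education, OR_E = 2.0 for higher versus lower education, and a share of healthy alters that differs by 10 or 20 points around 0.5. The count K has between-group variance (4d)² × 0.4 × 0.6 and within-group variance 4 × mean of p(1 − p).

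- d = 0.10: variances 0.0384 and 0.990; r = √(0.0384/1.0284) = 0.193; SD ratio √(0.24/1.0284) = 0.483. At ρ = 0.5, the coefficient is 0.483 × 0.193 × 0.75 / (1 − 0.0093) = 0.0707, and exp(0.0707 × 0.693) = 1.05.
- d = 0.20: variances 0.1536 and 0.960; r = 0.371; SD ratio 0.464. At ρ = 0.5, the coefficient is 0.464 × 0.371 × 0.75 / (1 − 0.0345) = 0.134, and exp(0.134 × 0.693) = 1.10.
- At ρ = 0.9, the same steps with 1 − ρ² = 0.19 give coefficients 0.018 and 0.037, so OR 1.01 and 1.03. At ρ = 1 the bias is zero.

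Simulation of this setting (1,500 runs per cell, 450 or 585 patients, ρ = 0.5) gives the same 1.05 to 1.10, with a false-positive rate of 8.5% to 21.5% against a nominal 5%. With education OR 1.5 the rate is 6% to 12%; with 2.5 it is 10% to 34%. With education in the model, the OR is 0.99 to 1.01 and the rate 4% to 7%. That last result follows from the set-up, since education is the only confounder simulated.

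**The case against.** The strongest reply is that SES is already in the models. If SES is built from education, nothing is lost. That stands as a possibility: the article does not define SES, and an article may leave the definition to a fuller document that is not shown here. But it lists education and SES as two measures, so a reader cannot assume that one contains the other.

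Second, the simulations are thinner than the planned models. Patient activation, therapy adherence, depressive symptoms and the other covariates may absorb part of the education effect. Only the healthy-alter count at one time point was simulated. Nothing was computed for connected alters, alters with medical knowledge or either change analysis, and the first change approach adjusts for the baseline outcome, which should remove much of a stable education effect. All of this stands and limits the size.

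Third, the work is exploratory. That lowers the stakes but does not justify omitting a measured candidate confounder from models meant to control confounding.

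Two stronger readings are tempting. A reader might infer that clustering by education will be reported as a network effect, or that similarity in education alone would support the hypotheses. The documents do not support this: SES is adjusted for, and even at the assumed correlation of 0.5 with education OR 2.0, about 80% to 90% of simulated studies showed no false signal. A reader might also see an internal contradiction with the practice-nurse models, which do name education. That list concerns the professional's own education, in a different population and without SES, so it is a contrast and not an inconsistency. Nor does the text promise complete education data for every patient; it plans questionnaire collection.

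**Conclusion.** The point holds in limited form. Educational level is the only listed patient descriptor left out of a closed covariate list, without explanation, although the models are meant to control confounding. What follows is possible residual confounding, not a demonstrated bias. Its size depends mainly on how far SES stands in for education, which the article does not say. On assumed inputs it runs from nil to modest: no bias if SES contains education, a spurious OR of about 1.01 to 1.03 per healthy alter at a correlation of 0.9, and about 1.05 to 1.10 at 0.5, both with education OR 2.0. The baseline-adjusted follow-up models are probably less affected. This is an inexpensive improvement to the plan and does not threaten the study.

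**What to change.** In Statistical analyses, add educational level as a categorical covariate to the patient models for physical activity, diet, smoking, SBP, cholesterol and risk score, and to the corresponding follow-up and change models, unless SES as defined already includes it. In that case, state the definition of SES and say that education is part of it.

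The cost is one to three degrees of freedom per model and some collinearity with SES. The collinearity affects the precision of the education and SES coefficients, which are not of interest in themselves. No new data are needed, as collection is already planned. The change is best made before outcomes are seen, because a covariate added later can look data-driven. It will not remove other ways in which people choose contacts like themselves, so the network coefficients should still be reported as associations.

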### Research aims

The overall aims of the study are:

1. To describe social networks of health care professionals in primary care involved in CVRM as well as those of patients with established CVD or a high risk thereof using a social networks approach.

2. To explore which characteristics of social networks are linked to key aspects of the delivery of high-quality CVRM (that is, providing advice and recommended treatment) and of patients’ self-management.

3. To explore the influence of several network characteristics on changes in delivery of high-quality CVRM and in patient’s self-management.

4. To evaluate different methods for including patients in a study of social networks.

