#### Hypotheses on health professionals

Patients are more likely to receive recommended CVRM and reach CVRM targets in general practices which have social networks characterized by: high density, high frequency of contact, high homogeneity, an appointed CVRM-coordinator who has a high degree of centrality, and a consistently identified opinion leader for CVRM.

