#### Hypotheses on patients

Patients are more likely to have favorable self-management and reach CVRM targets if they have social networks which contain: a high number of individuals with adequate self-management, a high number of individuals with adequate self-management who are connected to each other, few individuals with depressive symptoms, and individuals who provide access to individuals who can provide information on CVRM, particularly health professionals (such as nurses or physicians).

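### The three-category change model states no baseline term, so a network characteristic linked to baseline adequacy has its odds ratio attenuated, and reversed if the baseline gap is large

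*Protocol article*

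**What the plan says.** Under Research aims, the third aim is "To explore the influence of several network characteristics on changes in delivery of high-quality CVRM" and in patients' self-management. The Statistical analyses section answers it in two ways: "Two approaches will be used to investigate effects of social network characteristics on change in professional performance of practice nurses" and in patients' self-management and health outcomes.

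- **First approach.** The follow-up outcome is the dependent variable: "We will estimate similar models as described above and include baseline measures of outcomes of interest as predictors".
- **Second approach.** "Second, we will consider change as the difference between the baseline- and follow-up measures of the diverse outcomes of interest". An ordinal logistic model is then fitted, "with change represented in three categories; a shift from inadequate to adequate outcomes, no change, and shift from adequate to inadequate outcomes".

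For the second approach the article states no baseline term, no stratification by baseline status and no restriction to patients able to make a given transition. The covariates listed for the patient models do not include the baseline outcome: "The regression models will be controlled for trial arm (intervention vs control group), patient group (high risk or established CVD), and several personal characteristics". Neither approach is called the main one, and nothing says what happens if they disagree.

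The hypotheses expect the same network characteristics to go with adequacy. For practices: "Patients are more likely to receive recommended CVRM and reach CVRM targets in general practices which have social networks characterized by" (five features follow). For patients: "Patients are more likely to have favorable self-management and reach CVRM targets if they have social networks which contain" (four features follow).

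**The concern.** The three categories rest on an adequate/inadequate dichotomy. From inadequate, a patient can only stay or improve. From adequate, a patient can only stay or worsen. The middle category therefore puts the stably adequate together with the stably inadequate.

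This would matter little if baseline adequacy were unrelated to the network characteristic. The hypotheses say it is related. Patients with the favourable characteristic would then more often start adequate, with less room to improve and more room to worsen. The ordinal odds ratio picks up that difference in starting position along with any association between the characteristic and the transitions themselves. The outcome sections for professionals and for patients both describe effects on change as of main interest, so a weakened or reversed estimate would bear on a stated aim.

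**Working it through.** **Inputs.** The article gives no baseline adequacy, no transition rates and no sample size for this analysis (its 338 patients concern response rates to the invitation). Everything below except the model form is assumed. Let *b* be the proportion adequate at baseline, *i* the proportion of the inadequate who improve and *w* the proportion of the adequate who worsen.

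- Characteristic absent: *b* = 40%, *i* = 20%, *w* = 15%.
- Characteristic present: *i* = 30%, *w* = 10%, with *b* varied.

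**Conditional effects.** Both favour the characteristic.

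- Improving: (0.30/0.70)/(0.20/0.80) = 1.71.
- Staying adequate: (0.90/0.10)/(0.85/0.15) = 1.59.

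**What the ordinal model sees.** P(improve) = (1 − *b*)·*i* and P(worsen) = *b*·*w*. With the characteristic absent these are 0.60 × 0.20 = 12% and 0.40 × 0.15 = 6%. The ordinal odds ratio is the proportional-odds fit to these population probabilities, with no baseline term.

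| *b*, characteristic present | P(improve) | P(worsen) | Ordinal OR |
|---|---|---|---|
| 50% (10-point gap) | 0.50 × 0.30 = 15% | 0.50 × 0.10 = 5% | 1.27 |
| 55% | 13.5% | 5.5% | 1.13 |
| 60% (20-point gap) | 12% | 6% | 1.00 |
| 65% | 10.5% | 6.5% | 0.88 |
| 70% (30-point gap) | 0.30 × 0.30 = 9% | 0.70 × 0.10 = 7% | 0.77 |

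Hand check of the last row:

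- Improving against the rest: (0.09/0.91)/(0.12/0.88) = 0.73.
- Not worsening against worsening: (0.93/0.07)/(0.94/0.06) = 0.85.
- The fitted 0.77 lies between the two.

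**No conditional effect.** Set *i* = 20% and *w* = 15% in both groups, with 40% adequate at baseline in the comparison group.

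- 10-point gap: improvement 10% against 12%, worsening 7.5% against 6%, ordinal OR 0.80.
- 20-point gap: improvement 8% against 12%, worsening 9% against 6%, ordinal OR 0.64.

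**Sensitivity to the assumed rates.** Take *i* = 25% and *w* = 20% with the characteristic absent, and a common conditional OR of 1.5. Baseline adequacy is shown as absent/present.

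| Baseline adequacy | Ordinal OR, no baseline term |
|---|---|
| 50%/50% | 1.42 |
| 45%/55% | 1.13 |
| 40%/60% | 0.89 |
| 35%/65% | 0.70 |
| 30%/70% | 0.54 |

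Conditioning on baseline returns 1.50 in every row. Three other assumed pairs of rates (15%/10%, 40%/20%, 20%/40%) give 1.06 to 1.17 at 45%/55% and 0.83 to 0.94 at 40%/60%. The crossing point moves with the conditional effect. At 25%/20%, a conditional OR of 1.3 already gives 1.00 at 45%/55%, while a conditional OR of 2.0 still gives 1.12 at 40%/60%.

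**Net change in the 30-point example.** Adequacy goes from 40% to 40 + 12 − 6 = 46% without the characteristic, and from 70% to 70 + 9 − 7 = 72% with it. The net gains are 6 and 2 points, so an ordinal odds ratio below 1 describes net change correctly.

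**The case against.** Four points can be made for the plan.

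1. **A sound analysis is already there.** The first approach conditions on baseline, so the third aim does not rest on the ordinal model. This stands and lowers the weight of the point. It does not remove it, because the two approaches have equal standing.
2. **The ordinal model is not simply wrong.** It follows net change. In an observational study the network may itself have shaped baseline status, so the baseline-conditional odds ratio is not automatically the true effect. This stands: the two analyses answer different questions. A reader might infer that conflicting results would be beyond interpretation, but the disagreement can be explained. What the article lacks is a statement of which question is the main one.
3. **Reversal needs a large gap.** A reader might infer that a beneficial characteristic would generally come out as harmful under the study's own hypotheses. The article does not support that. The hypotheses give a direction and no size, and a modest gap attenuates the estimate without reversing it at the effects of about 1.6 to 1.7 used above. Nor can a frequency of wrong-sign results be given in general. It would depend on the assumed rates, on practice-level predictors varying over only 30 practices, and on how many patients accept the network invitation (50% and 65% are assumed for the two invitation groups).
4. **The baseline term may be in the full plan.** The article is condensed and lists no covariates specifically for the second approach. That is possible, but the outcome coding is fixed in the text, and the sentence adding baseline measures belongs to the first approach.

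A reader might also infer that one proportional-odds effect cannot hold for both transitions. That is not so: a common conditional odds ratio of 1.5 is recovered once baseline is conditioned on. The weakness is the missing conditioning.

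**Conclusion.** The point holds as a minor improvement to an exploratory aim. As written, the ordinal change model pools patients who can only improve with patients who can only worsen, and its odds ratio depends on how baseline adequacy differs across the network characteristic. With conditional odds ratios of about 1.6 to 1.7 and 40% baseline adequacy in the comparison group, the estimate is attenuated at a 10-point gap, vanishes at about 20 points and reverses only beyond that. Smaller conditional effects reverse at smaller gaps and larger ones at larger gaps. With no conditional effect, a 10-point gap alone yields about 0.80. All these figures rest on assumed rates and ignore clustering by practice, which affects precision more than the direction of the shift. The two approaches may disagree because they address different questions, and the article gives no precedence between them.

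**What to change.** Change the wording of the analysis in two places.

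- Name the first approach, the follow-up outcome adjusted for its baseline value, as the main analysis of change.
- Replace the pooled ordinal model with two logistic transition models using the same covariates: becoming adequate among those inadequate at baseline, and remaining adequate among those adequate at baseline.

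Adding baseline status to the ordinal model would also remove the distortion in the example. But one category is impossible in each baseline stratum, so the baseline coefficient diverges; separate transition models are cleaner.

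No new data are needed. The cost is precision, because each transition model uses only part of the sample. With 900 patients and an assumed 40% adequate at baseline, that is 540 for becoming adequate and 360 for remaining adequate, before non-response.
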